**Baseline Data:**

- Baseline annualized rate of the primary outcome in the resident's facility (last 3 years)
- Age
- Gender
- Location (Calgary / Edmonton / Other)
- Level of Care Designation (Long Term Care, Long Term Care-Dementia, Supportive Living, Supportive Living-Dementia, Personal Supportive Living)
- Length of stay in LTC facility
  - New admission (last 60 days)
  - Old Admission ( $\geq 3$  years)
- Charlson score

- Key Comorbidities - requiring 2 claims or 1 in-hospital diagnosis (any Dx, not just primary Dx) over the duration of available administrative claims:
  - Diabetes
  - Coronary Artery Disease (CAD)
  - Stroke
  - Osteoarthritis (OA)
  - Congestive Heart Failure (CHF)
  - Chronic Obstructive Pulmonary Disease (COPD)
  - Hip Fracture – for this characteristic only 1 diagnosis is required
  - Chronic Kidney Disease (CKD) – for this characteristic only 1 diagnosis is required (since family physicians rarely have CKD dedicated visits), or 2 GFR < 40
  - Dementia
  - $\geq 2$  of the above Key comorbidities
- TIA (1 claim or 1 in-hospital Dx)
- Stroke or TIA (1 claim or 1 in-hospital Dx)
- Dialysis (1 procedure)
- Total number of medications
- Total number of BP medications
- Days in hospital in prior 6 months
- Number of ER visits in prior 6 months
- *Collected for the purpose of inclusion / exclusion*
  - *Hypertension (2 claims or 1 in-hospital) – inclusion criteria*
  - *Any once daily hypertension medication – inclusion criteria*
  - *Glaucoma – exclusion*

#### **D) Power/Sample Size Estimate:**

Expected Recruitment: At the time of this application we are collaborating with multiple ICCER-affiliated LTC organizations that wish to participate in this initiative. Most of these organizations have multiple facilities, many of which have multiple buildings or wings. Using Canadian Primary Care Sentinel Surveillance (CPCSSN) EMR data (accessed for the purpose of this application) we know that 53% of Canadians 80 yrs and older are listed as currently taking daily BP lowering medication. In our experience most of these medications are maintained upon nursing home admission. This suggests, given the 18-month median lifespan of newly admitted patients (and 9 month median lifespan of those already resident at the time of the study), that we should easily obtain 1200 residents total over the roughly 2-3-year duration of the trial.

Power: Utilizing well described methods for sample size determination, inflating the number of events to account for noncompliance, conservatively setting the median lifespan at 3 years to account for the inclusion of supportive living residents who, on average, live longer than the expected 18 months in long-term care facilities and assuming 33% of patients will be censored prior to any events, we find that 1232 patients would have 80% power (at a p of 0.05) to detect a difference between groups in the primary outcome of 27.6%. Although smaller differences would still be clinically meaningful, this difference is less than the 55% relative reduction in total mortality claimed in the MAPEC trial that we are trying to reproduce, and it is a very conservative minimum estimate for the actual power that the study will have. Additional power, while not directly calculable, will come in 2 ways: 1) These calculations assume no meaningful covariates and we have several covariates that are likely to be predictive of each outcome – in particular the resident's

level of care designation, and 2) we will continue to seek new facilities to partner with over the course of the trial – which should increase the number of residents available.

Overall: We expect to randomize a minimum of 1200 residents and observe over a roughly 2-3 year period until 301 primary outcomes have occurred (with those outcomes being reported to us quarterly by the Alberta SPOR Data Platform). At a minimum this will provide sufficient power (80% power to detect a 27.6% difference) to validate or refute the MAPEC trials claim of a 55% reduction in mortality, and will likely provide substantial additional fidelity to detect smaller differences that are not currently calculable (as a result of meaningful covariates, continuous outcomes, and the expectation of additional facilities joining the project in coming months).

**E) Confirmation of data accuracy:** Prior to randomization the data steward will produce a list of all residents they believe to currently reside at each of the participating facilities. They will simultaneously request a list of all admitted residents from each participating facility and will compare these two lists to ensure there are no errors in identifying residents.

**F) Recruitment / Patient Flow:** (Flow Diagram - appendix pg. 6)

1. Informing Patients / Families / Primary Care Providers: Prior to facilities being randomized, we will send letters to all next of kin, and all attending primary care providers, notifying them that this study is taking place and that blood pressure medications might have their timing switched to bedtime. If family or physicians object, we will ask them to e-mail or call a toll free number to let us know the resident's name and the facility they reside in and we will exclude them from the timing change. A number will also be provided to speak with a BedMed physician if families or physicians have questions about the study.
2. Randomization: A minimum of one month after the last notification letter is mailed, eligible residents who have not opted out of participation will be randomized using random blocks of 2 or 4 with no stratification.
3. Implementing the Intervention: Each facility's pharmacist will be in charge of implementing the intervention. The pharmacy will receive a list of eligible residents directly from the AHS biostatistician supporting the study using an e-mail with a secure link. Only once a day BP medications will be changed and the recommendation is to change BP medications in the order ABCD-O (Angiotensin Inhibitor / Angiotensin Receptor Blocker, Beta-Blocker, Calcium Channel Blocker, Diuretic, Other). If there are multiple once daily BP medications, only one timing change will be made per week. If the pharmacist is aware of any clinical reason why a particular timing would be better they will follow their clinical judgment. Patients with known glaucoma, or who use glaucoma medications, will keep to morning BP medications. A BedMed physician will be available 24 hours for pharmacist questions related to timing changes.
4. Study Follow-up: Post implementation of the intervention, the study team will monitor administrative claims and RAI-MDS data quarterly. The study will end once 301 primary outcome events have been observed.

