# BedMed-Frail Statistical Analysis Plan

## **Adaptive Randomization (conversion to modified intention-to-treat)**

Participating facilities are volunteering to support our trial with no financial compensation, and “fitting it in” with other work. For several facilities, COVID-19, other infectious outbreaks, and implementation of other facility initiatives has led to long delays before the facility pharmacist was able to act on their allocation list. For a few facilities this delayed implementation by several months. Given 1) we are placing an equal emphasis on detecting harm, 2) long implementation delays make both groups look more similar and reduce the ability to detect harm, and 3) no action of any kind was taken related to the facility’s allocation list in this interval, we have adapted the trial to consider the date of each facility’s initial randomization to be the date the allocation list was actually acted upon, and not the date it was generated. This date was determined by the AHS data analyst, using electronic pharmacy dispensing data, to be the day before the first switch of an eligible patient’s BP medications from morning to bedtime. Individuals who, on the date of implementation, were no longer resident in the facility, hospitalized, or without once daily BP meds, were excluded from the trial.

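### The 301-event stopping target equals the two-sided event count for a 27.6% reduction before any inflation, so the stated noncompliance allowance is not visible in it

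*Combined protocol and SAP*

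**What the plan says.** The power paragraph of the protocol (section D, Power/Sample Size Estimate) lists its ingredients as "inflating the number of events to account for noncompliance, conservatively setting the median lifespan at 3 years", plus 33% of patients censored before any event. It concludes that 1232 patients give "80% power (at a p of 0.05) to detect a difference between groups in the primary outcome of 27.6" per cent. It calls this result conservative: "it is a very conservative minimum estimate for the actual power that the study will have". Two sources of further power are named: prognostic covariates, which the calculation leaves out, and recruitment of more sites ("we will continue to seek new facilities to partner with over the course of the trial").

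The Overall paragraph of the same section ties 301 primary outcomes to "80% power to detect a 27.6% difference". The Outcomes paragraph of section C sets the same count as the end of the trial, and section F (Study Follow-up) repeats it: "The study will end once 301 primary outcome events have been observed".

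The documents supplied give no noncompliance rate, event count before inflation, formula or sidedness, and do not say whether 27.6% is a hazard reduction. On adherence, the waiver-of-consent section lets patients and providers return to morning dosing without giving a reason. Section F lets the pharmacist follow clinical judgement on timing. The SAP (Nonadherence) keeps nonadherent residents in all planned analyses.

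**The concern.** If events were inflated for noncompliance, the stopping target should exceed the number a textbook formula gives for the same effect, error rate and power. It does not: the two agree to the event.

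This matters because the design is event-driven. Power for the primary outcome depends on the number of events at analysis, so an allowance held only in the patient number disappears when the trial stops at event 301. Some nonadherence is permitted by design, and nonadherent residents stay in the analysis, so the intention-to-treat effect will be smaller than the full-adherence effect. A reader told that 80% is a conservative minimum, with noncompliance already covered, would credit the trial with more ability to detect a true 27.6% reduction than it has.

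**Working it through.** **Inputs.** Protocol section D: p of 0.05, 80% power, 27.6% difference, 301 events, no covariates assumed. Section F: random blocks of 2 or 4, so 1:1 allocation. Plan for Data Analysis: proportional hazards model. My assumptions: 27.6% means HR = 1 - 0.276 = 0.724, and the test is two-sided.

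**1. Reproducing 301.** Schoenfeld, 1:1: events = 4(z_α/2 + z_β)² / (ln HR)².

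- (1.95996 + 0.84162)² = 7.8489
- (ln 0.724)² = 0.10431
- 4 × 7.8489 / 0.10431 = 300.995, rounded up to 301

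In reverse, exp(-2 × 2.80158 / √301) = 0.7240. Only 300, 301 or 302 events give a detectable reduction that rounds to 27.6%, so chance agreement is implausible. Power at 301 events is 80.00%, with no reserve. (Freedman's formula gives 306.2, rounded up to 307, so it does not explain 301 as an inflated number either.)

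**2. Other readings.**

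- One-sided 5%: 4(1.64485 + 0.84162)² / 0.10431 = 237.1, i.e. 238 events. Then 301 would carry a factor of 301/237.1 = 1.27, or about 11% noncompliance, since 1 - √(237.1/301) = 0.112.
- 27.6% read as HR 1.276: 529 events, which does not fit.

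**3. What an allowance would look like.** With net adherence a (the share of the full between-group contrast that is achieved), events = 301/a². The levels of a are assumed.

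**4. Power if the trial stops at 301.** Power = Φ(½√301 × |ln HR_a| - 1.96), under two dilution models: linear, HR_a = 1 - 0.276a, and log-HR, HR_a = 0.724^a. For a = 0.9 these give HRs of 0.7516 and 0.7478, so Φ(0.517) = 0.697 and Φ(0.561) = 0.713.

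**5. Full-adherence reduction that dilutes to 27.6%.** Linear: 0.276/a. Log-HR: 1 - 0.724^(1/a).

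| Net adherence (assumed) | Events for 80% power, 301/a² | Power at 301 (linear / log-HR) | Full-adherence reduction with 80% power at 301 (log-HR / linear) |
|---|---|---|---|
| 100% | 301 | 80.0% / 80.0% | 27.6% / 27.6% |
| 95% | 334 | 75.1% / 75.9% | 28.8% / 29.1% |
| 90% | 372 | 69.7% / 71.3% | 30.2% / 30.7% |
| 80% | 471 | 58.1% / 61.1% | 33.2% / 34.5% |

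**6. The patient number.** Assuming 2 years of follow-up with the stated 3-year median, the two-arm average event probability is 0.327, and 301/0.327 is about 920 patients. Allowing for 33% censoring gives about 1224 (× 1.33) or 1373 (/ 0.67). The 1232 therefore shows no clear extra allowance for noncompliance, although this depends on the assumed follow-up. Any allowance there would in any case be lost at event 301.

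**The case against.** The strongest reply is that absence is inferred. The protocol's hypothesis is directional, and a one-sided 5% test would leave a real inflation inside 301. This cannot be strictly excluded. But the objectives ask whether bedtime dosing alters outcomes, in either direction, and the SAP says "we are placing an equal emphasis on detecting harm". The two-sided formula also returns 301 exactly.

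A second reply is that 27.6% may already be the diluted difference, which would make 301 correct. The power section speaks of inflating events, not of diluting the effect, and gives no full-adherence effect. Even so, a reader would need to be told that the figure is an intention-to-treat one.

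A third reply is that covariate adjustment may recover power. That stands: the protocol names it, and the calculation omits it. But the protocol also says the gain cannot be calculated directly, so it cannot stand in for the stated inflation.

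Four stronger readings are tempting, and the documents do not support them:

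- **The SAP's 60% cut-off shows that low adherence is expected.** It is a facility-level share of doses at bedtime. The SAP's process outcome counts medications taken more than once a day as half morning and half evening, and the protocol leaves those medications and loop diuretics where they are. A fully compliant facility can therefore fall well short of 100%. The cut-off is not an adherence rate.
- **The claim about new facilities is wrong altogether.** It fails for the primary outcome, where added sites only bring event 301 sooner. It can hold for costs and the quarterly MDS outcomes, which the event count does not cap.
- **The trial cannot test the MAPEC claim.** Applying a 55% reduction to the primary outcome, 301 events give about 99.9% power at an assumed 80% net adherence.
- **Power collapses with any nonadherence.** At 1% noncompliance it is still about 79%. The loss becomes material at about 5-10%.

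**Conclusion.** Wrong as written. On the two-sided reading, the stopping target is the event count before inflation, and the allowance described in the power section is not in it. Before covariate adjustment, power for a true full-adherence reduction of 27.6% is below 80%: about 75-76%, 70-71% and 58-61% at 95%, 90% and 80% net adherence (linear to log-HR dilution).

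This rests on three assumptions: a two-sided test, 27.6% meaning HR 0.724, and illustrative adherence levels. It does not show that the sponsor never made an allowance, only that none can be found in the number that ends the trial. A reader might infer that a null result would be uninterpretable. That does not follow, because the confidence interval, not the design power, governs what a null result excludes.

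The finding concerns the 2019 protocol. Both supplements point to a final version published in 2023, which is not among the documents supplied.

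**What to change.** In protocol section D (Power and Overall), replace the power statement with wording such as:

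> 301 events give 80% power (two-sided 0.05, unadjusted) for a 27.6% reduction as observed under intention-to-treat, with no further allowance for noncompliance. This corresponds to a full-adherence reduction of about 30-31% at 90% and 33-35% at 80% net adherence (assumed levels; range over log-HR and linear dilution).

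If a real inflation was made, the sponsor should instead state the noncompliance rate, the sidedness and the event count before inflation, and say whether 27.6% is before or after dilution. Otherwise:

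- Remove the statement that events were inflated.
- Replace the description of the estimate as a very conservative minimum with a statement that only covariate adjustment may add power for the primary outcome.
- Limit the new-facilities claim to outcomes not capped by the event count (costs, MDS outcomes), and note that for the primary outcome more sites only shorten the time to event 301.

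The cost is wording only. The stated power becomes less favourable, and no extra patients are needed.

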## **C) BEDMED-Frail TRIAL PROTOCOL:**

**Design:** Event-driven Prospective Randomized Open Blinded End-Point (PROBE) Randomized Trial.

**Population:** Hypertensive long-term care (LTC) residents using BP lowering medication.

**Inclusion Criteria:** 1) Hypertension diagnosis as indicated by  $\geq 2$  such billing diagnoses at any time in the administrative claims data by any provider; 2)  $\geq 1$  ONCE DAILY BP lowering medication; 3) LTC resident in a participating facility.

**Exclusion Criteria:** 1) Personal history of glaucoma or use of glaucoma medications. *Glaucoma is an exclusion because nocturnal hypotension (i.e. excessively low blood pressure while sleeping) has been associated with ischemic optic neuropathy in such patients.* 2) Any family member or treating physician (all of whom will be notified of the LTC facilities participation in this initiative) requesting the patient not participate.

**Intervention:** Switching (*one at a time as tolerated*) one or more morning BP meds to BEDTIME (or *maintaining* bedtime BP meds if already taken at that time). The timing of loop diuretics (which can cause meaningful diuresis), and BP medications taken more than once a day, will not be altered. If more than one medication change is needed, each change will take place one week apart.

**Comparator:** Maintaining (or switching to) morning BP medication use.

**Outcomes:** Outcomes are drawn from administrative claims data and quarterly MDS reporting. The Alberta SPOR Data Platform will monitor our primary outcomes quarterly during the trial, and the trial will conclude once 301 participants have experienced primary outcome events. Outcomes include:

- Primary: Composite of all-cause death and hospital admission or emergency room visit for acute coronary syndrome/MI, heart failure, or stroke (using administrative data based case definitions with validated coding algorithms).
- Secondary: 1) Each element of the primary outcome alone; 2) All-cause hospitalization; 3) Acute Care Costs (from each admissions resource intensity weight & length of stay).

*The following additional outcomes (unless otherwise indicated) will be determined from the first available **MDS Quarterly assessment** in the 3 - 6 month window post randomization:*

- Safety: 1) Fell (past 30 days); 2) Any Fracture (from administrative claims data over the study duration – not MDS data); 3) Full Thickness Skin Ulceration (stage 3 or 4).

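### The 301-event stop carries no visible noncompliance inflation for the quoted 27.6%, so 80% power holds only if 27.6% is the diluted intention-to-treat effect

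*Combined protocol and SAP*

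**What the plan says.** Section D (Power/Sample Size Estimate, Power paragraph) lists the ingredients of the calculation. They include "inflating the number of events to account for noncompliance" and "assuming 33% of patients will be censored prior to any events". The section concludes that "1232 patients would have 80% power (at a p of 0.05") to detect a 27.6% between-group difference in the primary outcome. It compares that figure directly with the 55% mortality reduction claimed by the earlier trial and adds that "it is a very conservative minimum estimate for the actual power that the study will have". It names two unquantified sources of extra power: prognostic covariates and recruitment of further facilities.

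The stopping rule appears three times. Section C (Outcomes) says "the trial will conclude once 301 participants have experienced primary outcome events". Section D (Overall) says follow-up runs "until 301 primary outcomes have occurred" and ties this to "80% power to detect a 27.6% difference". Section F, item 4, says "The study will end once 301 primary outcome events have been observed".

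No noncompliance rate, inflation formula, pre-inflation count or full-adherence effect is given anywhere. The SAP supplied has no sample-size section. Its Nonadherence paragraph keeps nonadherent residents in all planned analyses, so the primary estimate is open to dilution.

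**The concern.** If events were inflated for noncompliance, the stopping target should exceed the plain event count for the quoted effect. It does not: the two agree to the nearest event. Either the inflation never reached the number that stops the trial, or 27.6% is already a diluted effect and the larger full-adherence effect behind it is not disclosed.

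In an event-driven trial the event count governs power, so the distinction matters. Some noncompliance is expected by design. Residents and providers may change the timing back without giving a reason (waiver-of-consent section, item 5), and pharmacists may follow their own clinical judgement (Section F, item 3). What is at stake is how a null result is read. Someone relying on Section D could say that a 27.6% benefit of bedtime dosing, if actually taken at bedtime, had been excluded with 80% power. On the plainer reading of the text the trial could not support that.

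**Working it through.** **Inputs from the protocol.** Power is 80% and alpha 0.05 (Section D). Sidedness is not stated. Allocation is 1:1, implied by blocks of 2 or 4 (Section F, item 2). The effect is 27.6%, read as a hazard ratio (HR) of 1 − 0.276 = 0.724. The analysis is proportional hazards (Plan for Data Analysis). The stopping target is 301 events.

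**Input assumed.** The noncompliance proportion c is taken as 5% to 40%, because the documents give no rate.

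**Step 1: reproduce 301.** Schoenfeld's formula for 1:1 allocation is

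D = 4(z₀.₉₇₅ + z₀.₈₀)² / (ln HR)² = 4(1.960 + 0.8416)² / (ln 0.724)² = 300.995, which rounds up to 301.

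The match is exact with no inflation factor. Freedman's formula gives 307. A one-sided test gives 238 (Schoenfeld) or 242 (Freedman), so the two-sided Schoenfeld calculation is the one that fits. Power at 301 events for HR 0.724 is 80.0%.

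**Step 2: suppose 27.6% is the full-adherence effect.** Let noncompliance shrink the log hazard ratio by (1 − c). Then

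- power = Φ(0.32296 × (1 − c) × √301 / 2 − 1.960)
- events for 80% power = 300.995 / (1 − c)², rounded up

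**Step 3: suppose 27.6% is already diluted.** The full-adherence reduction detectable with 80% power is 1 − 0.724^(1/(1 − c)).

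| Assumed c | Step 2: power at 301 events | Step 2: events for 80% | Step 3: full-adherence reduction |
|---|---|---|---|
| 0% | 80.0% | 301 | 27.6% |
| 5% | 75.9% | 334 | 28.8% |
| 10% | 71.3% | 372 | 30.2% |
| 20% | 61.1% | 471 | 33.2% |
| 40% | 39.0% | 837 | 41.6% |

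Diluting the 27.6% linearly instead of on the log scale gives slightly lower power in Step 2: 69.8% at 10% and 34.9% at 40%.

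**Step 4: the earlier trial's 55% reduction.** At c = 40% the diluted HR is 0.45^0.6 = 0.619, and power at 301 events is 98.6%.

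**Step 5: can 301 be an inflated count for some other effect?** Yes. HR 0.65 needs 169.2 events. Allowing for 25% noncompliance gives 169.2 / 0.75² = 300.8, so 301, and the diluted HR is 0.65^0.75 = 0.724. The arithmetic alone cannot say which effect 27.6% represents.

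**The case against.** The strongest reply is that 27.6% is described as a difference between groups, which can naturally mean the difference the trial would observe. On that reading 301 events do give 80% power, and Step 5 shows that a properly inflated calculation reported on the diluted scale would also land on 301. This stands. A reader might infer that the stated power is simply not delivered, but the documents do not settle that. The text does lean the other way: it says the events were adjusted, not the effect, and it sets 27.6% beside the 55% claim without mentioning dilution.

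Two stronger inferences fail.

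- Taking the 33% censoring literally, a reader might compute 1232 × 0.67 = 825 events and back out about 40% planned noncompliance. The same sentence sets a 3-year median lifespan, and Section D expects roughly 2–3 years of observation. If that median drives the event rate, at most half would have an event by 3 years (616 of 1232). Treating the 33% as attrition, with a 2-year control event probability of 37.0%, gives 1232 × 0.67 × 0.370 = 305, close to 301.
- A reader might take the SAP's 60%-of-doses facility cut-off as evidence of 40% noncompliance. That cut-off is a share of doses. Drugs given more than once daily count as half morning and half evening, and the intervention asks for only one or more drugs to be moved. A resident can comply with well under 100% of doses at bedtime.

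It is also fair that the SAP limits dilution, by starting the clock at implementation and by censoring residents who change facility. Covariate adjustment may add some power as well. The plan quantifies neither. Finally, the final protocol was published separately and is not among the documents reviewed, so it may restate the calculation.

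**Conclusion.** The concern holds in conditional form. The stopping count is the uninflated two-sided count for the quoted effect, and the statement that events were inflated cannot be reconciled with it unless 27.6% is the diluted effect. Under the plainer reading, power falls to about 76%, 71%, 61% and 39% at 5%, 10%, 20% and 40% noncompliance. Under the other, 80% power is correct but refers to an undisclosed full-adherence reduction of 30.2% to 41.6% at 10% to 40%. These figures rest on assumed rates, log-hazard-ratio dilution and no covariate gain.

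On neither reading do the documents support calling the figure a very conservative minimum. Further facilities cannot raise power under a fixed 301-event stop: they add no events and only bring the target sooner. The comparison with the 55% reduction is unaffected. The problem lies in the stated power and in what a null result may be said to exclude. The analysis method and the event target are not at fault, so this should be corrected but is not critical.

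**What to change.** Keep 301 events and restate the Power and Overall paragraphs of Section D:

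1. Say that 301 events give 80% power (two-sided 0.05) for a 27.6% hazard reduction as observed under intention-to-treat, with no further allowance for noncompliance.
2. Beside it, give the matching full-adherence reduction, or the power if 27.6% is meant as the full-adherence effect, over a stated range of noncompliance. The table above could be used.
3. Delete the statement that events were inflated, or show the noncompliance rate and the event counts before and after inflation.
4. Delete the description of the figure as a very conservative minimum and the claim that new facilities add power.
5. Say what the 33% censoring refers to, so that a reader can connect 1232 residents with 301 events.

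The cost is wording only. No residents or events are added and no analysis changes. The downside is a less favourable power statement.
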